#### Chemotherapy regimen

The investigator is responsible to decide whether adjuvant chemotherapy or neoadjuvant chemotherapy is suitable for the patients according to the CACA Guidelines for Breast Cancer Diagnosis and Treatment (2015 Edition) and NCCN Clinical Practice Guidelines in Oncology: Breast Cancer (Version 3. 2015). Choices of chemotherapy regimens include anthracycline (EC × 4 times, CEF × 6 times), taxanes (TC × 4–6 times, P × 4–6 times), anthracycline combined taxanes (TAC × 6 times, FEC × 3 followed by T × 3 times, AC × 4 followed by T × 4 times, AC × 4 followed by wP × 12 times, ddAC × 4 followed by wP × 12 times), and others (PC × 4–6 times, DP × 4–6 times, NX × 4–6 times, X × 4–6 times).

### Criteria for discontinuing or modifying allocated interventions {11b}

Participants who show any adverse effects will be reported and followed up by their responsible physicians. A reduction in dose or discontinuation of treatment will be decided by the physician according to the CACA Guidelines for Breast Cancer Diagnosis and Treatment (2015 Edition) and NCCN Clinical Practice Guidelines in Oncology: Breast Cancer (Version 3. 2015), or upon participant request. Outcome data will be collected as usual according to the protocol for these participants.

### Strategies to improve adherence to interventions {11c}

To improve the adherence and promote participant retention, the required amount of moxa sticks and TCM granule will be provided by the Central Pharmacy of Yueyang Hospital to the corresponding participants each time after receiving chemotherapy, for free. For participants who decide to discontinue the treatment and withdraw from the study, they will be asked to fill a questionnaire to simply explain the reason behind. After discontinuation, outcome data will not be collected for these participants.

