## Interventions

### Explanation for the choice of comparators {6b}

The control group is treated routinely without either TCM decoction or moxibustion. Both the MD and MP groups are treated with moxibustion. The MD group is additionally treated with TCM decoction, while TCM placebo is provided to the patients in the MP group.

The TCM placebo which is made of excipients and flavouring agents is used as a comparator. The packaging, shape, weight, odour, and colour of the placebo are identical to that of the Wenshen Shengbai Decoction. The placebo is manufactured by Jiangyin Tianjiang Pharmaceutical Co., Ltd., and is stored and provided to the patients by the Central Pharmacy of Yueyang Hospital.

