### Methods in analysis to handle protocol non-adherence and any statistical methods to handle missing data {20c}

Two datasets will be generated for subsequent analysis: the intent-to-treat (ITT) population which includes all eligible participants and the per-protocol (PP) population which includes only participants who completed the trial.

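### Sections {11b} and {11c} conflict on outcome collection for participants who choose to stop the allocated treatment, and section {20c} ties ITT to eligibility and PP to trial completion

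*Protocol article*

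**What the plan says.** Section {11b} of the protocol article covers dose reduction or discontinuation decided by the physician under the cited guidelines, "or upon participant request". For all of these it states: "Outcome data will be collected as usual according to the protocol for these participants".

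Section {11c}, on adherence, describes the free supply of moxa sticks and granules and then turns to those who leave: "For participants who decide to discontinue the treatment and withdraw from the study, they will be asked to fill a questionnaire" giving the reason. It adds: "After discontinuation, outcome data will not be collected for these participants". Section {18b}, on retention and complete follow-up, only refers back to {11c}.

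Section {20c} defines two analysis sets: "the intent-to-treat (ITT) population which includes all eligible participants and the per-protocol (PP) population which includes only participants who completed the trial".

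On the arms, section {6b} says: "The control group is treated routinely without either TCM decoction or moxibustion". MD and MP both add daily self-moxibustion at home plus granules (active or placebo). Section {14} allows for one overall drop rate of 20%, not split by arm.

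**The concern.** The two rules meet in one kind of patient: the woman in MD or MP who tells her physician that she wants to stop the granules or the moxibustion. Under {11b} her outcomes continue to be recorded. Under {11c} they may end, because that section treats stopping and leaving as one decision and sets the cut-off at discontinuation, not at withdrawal of consent. Two physicians could handle the same request in opposite ways and both claim to follow the protocol.

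At stake are the primary outcomes on leukopenia, neutropenia and rhG-CSF use, and later the 3-year DFS and OS. Weekly counts during chemotherapy are already scheduled for every patient, so this loss is avoidable. Data never collected cannot be recovered by an analysis plan. If loss is related to outcome and heavier in the moxibustion arms, the comparison with control is biased, and the sample size is built on that comparison.

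The set definitions add to this. A PP set chosen on completion selects on something that happens after randomisation. It does not ask whether the allocated granules or moxibustion were taken, which is what a per-protocol analysis is meant to address.

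**Working it through.** **1. The texts side by side**

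| Point | {11b} | {11c} |
|---|---|---|
| Who decides | physician or participant | participant |
| What happens | dose reduced or treatment stopped | treatment stopped and study left |
| Outcome data | continue | end after discontinuation |

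A patient who stops for medical reasons falls only under {11b}. A patient who explicitly leaves the study falls under {11c}. A patient who asks to stop treatment and says nothing about the study meets {11b}, but no section says that she may stop the granules or moxibustion and stay in. That is the overlap.

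**2. The plan's own sample size**

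Inputs from section {14}: 81% (control) and 52% (MD) with grade 2 or above suppression, margin 15 points, α = 0.05, drop rate 20%. Power is printed as 0.08 and is read here as 0.80.

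n = [0.81×0.19 + 0.52×0.48] × (1.645 + 0.842)² / (0.29 − 0.15)² = 127.3, so 128 per arm.

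128 × 1.2 = 153.6, so 154 per arm, and 3 × 154 = 462. This reproduces the stated figure, with α taken as one-sided.

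If 20% of each arm stop contributing data, 154 × 0.8 = 123 remain, slightly under 128. With outcomes on everyone, 154 remain.

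**3. Illustration of bias**

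These are assumptions, not figures from the article: no true effect (81% in both arms), control complete, and a fraction d lost from one moxibustion arm with true event rate q among those lost.

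Observed rate = (0.81 − d·q) / (1 − d)

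- d = 0.20, q = 0.90: (0.81 − 0.18)/0.80 = 78.75%, an apparent benefit of 2.25 points.
- d = 0.20, q = 1.00: (0.81 − 0.20)/0.80 = 76.25%, an apparent benefit of 4.75 points.
- d = 0.10, q = 0.91: (0.81 − 0.091)/0.90 = 79.9%, an apparent benefit of 1.1 points.
- q = 0.81 (loss unrelated to outcome): 81%, bias zero for any d.

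For a two-sided 5% test of two proportions (pooled variance, 154 control patients against those remaining), the chance of a false finding in favour of moxibustion is 2.5% without bias. It becomes 4.3% for d = 0.10, q = 0.91; 6.8% for d = 0.20, q = 0.90; and 16.1% for d = 0.20, q = 1.00.

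**4. The analysis sets**

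A patient who never used her granules but attended every visit is in PP. A patient who took everything as allocated and then missed later visits may be out, depending on what completing the trial means. The article does not say: the follow-up schedule section mentions 8 weeks, Table 3 runs to 36 months after chemotherapy, and the long-term efficacy section lists 10-year outcomes.

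**The case against.** The strongest reply is that there is no conflict. Section {11c} concerns people who stop and also withdraw, {11b} concerns people who only stop, and every participant may withdraw at any time (section {26a}). That is a natural reading, and it narrows the problem to participants who choose to stop. It does not remove it: {11b} includes requests by the participant, and {11c} ends collection at discontinuation without separating the two decisions.

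On ITT, the trial design section says that all eligible patients are divided into the three groups, so eligible can be read as allocated. No section permits exclusions after randomisation. This stands: the ITT wording is loose, and no exclusion is shown.

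A reader might infer that the ITT comparison does lose patients selectively from the moxibustion arms. The article does not support that. Section {20c} does not drop withdrawn patients from ITT; they stay in the set without later outcomes. No loss by arm is given. Control patients can stop chemotherapy or withdraw, and they know that they receive neither added treatment. MD and MP both have moxibustion and granules, so the mechanism mainly concerns comparisons with control.

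A reader might also infer that relapse or death removes a patient from PP. That depends on the undefined meaning of completing the trial and cannot be asserted.

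Finally, the illustration puts the whole 20% in one arm and none in control, whereas the plan has a single overall rate. Even then the bias is under 5 points, against an assumed difference of 29 points and a margin of 15. The 81% is the sample-size rate, which is not itself among the listed primary outcomes. All of this stands, so the figures show sensitivity to assumptions and are not evidence that bias is present.

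**Conclusion.** The point holds in limited form. Sections {11b} and {11c} conflict for participants who choose to stop the allocated treatment, and must be reconciled. If {11c} is followed, ITT members who stop will lack later outcomes, and the loss may, not will, be heavier in MD and MP than in control. The article cannot give its size. Under the one-arm 20% loss assumed above, the distortion is about 2 to 5 points. With equal loss unrelated to outcome it is zero, and the only cost is precision.

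The PP definition is a poor rule as stated, because it selects on completion and ignores receipt of the allocated treatment. The ITT wording is a lesser matter of clarity. Handling of missing values may be set out in an analysis plan that is not shown, and its absence here is not part of the point.

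**What to change.** Reconcile {11b} and {11c}. State that stopping granules or moxibustion is not withdrawal from the study, and that the outcomes already scheduled (weekly counts, rhG-CSF use, chemotherapy record, DFS and OS) continue to be collected. Collection should end only when the participant withdraws consent to further data collection, and the cut-off in {11c} should be tied to that event. This changes data collection only and leaves treatment decisions untouched.

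In {20c}, define ITT as all randomised participants, analysed in the arm to which they were randomised. Define PP by receipt of the allocated intervention during chemotherapy, not by completing the trial.

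The cost is an amendment to the protocol and consent wording, with no new visits or tests. The amended consent would not automatically reach patients already enrolled (218 by 8 December 2019, according to the trial status section).

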### Relevant concomitant care permitted or prohibited during the trial {11d}

No specific concomitant care and interventions are permitted or prohibited during the trial.

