## Trial design {8}

This study is a randomized controlled clinical trial single-blinded for TCM decoction but not moxibustion. Patients will be divided into groups by stratified randomized grouping. The stratification factors involve age (below 40s, 40s, 50s, 60s, or above), chemotherapy regimen (anthracyclines, taxanes, anthracyclines combined with taxane, and others), and chemotherapy strategy (adjuvant and neoadjuvant). All eligible patients are equally divided into the control group with no TCM decoction/moxibustion treatment (control), the TCM decoction combined with moxibustion group (MD), and the placebo combined with moxibustion group (MP). All participants are expected to treat with standard chemotherapy and rhG-CSF regimen. The detailed study flow is illustrated in Fig. 1. The clinical pathway of each participant is shown in supplementary figure 1. Patients or the public will not be involved in the design, or conduct, or reporting, or dissemination plans of our research.

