### Outcomes {12}

#### Primary outcomes

Primary outcomes are as follows:
The proportion of patients with relief of leukopenia and/or neutropenia.The number and proportion of patients with relief of myelosuppression-associated SAE, defined as grade 3–4 leukopenia and/or neutropenia and FN.The median and mean duration time of relief of leukopenia and/or neutropenia.The dosing of rhG-CSF.

The grading of adverse reactions is in accordance with the CTCAE 4.0.2 criteria. Leukopenia is defined as an abnormal decrease in white blood cells of less than LLN-3.0 × 10^9^/L. Neutropenia is defined as an abnormal decrease in netrophils of less than LLN-1.5 × 10^9^/L. The definition of FN is based on the IDSA guidelines (American Society of Infectious Diseases Guide 2010 edition), which is an absolute neutrophil count (ANC) of < 500 neutrophils/mcL or an anticipated decline to ≤ 500 in the next 48 h and progress to ≥ 38.3 °C orally or ≥ 38.0 °C for a duration over 1 h.

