### Sample size {14}

In previous studies, the incidence rate of myelosuppression was 81.0% in the control group and 61.7% in the TCM decoction group [29]. The cure rate and effective rate of the moxibustion group were 84.1% and 66.4%, while those of the control group were 35.2% and 33.3% [30]. In our preliminary study, the bone marrow suppression rate (grade 2 or above) was 52% and 81% for the MD group and the control group, respectively (δ = 15%in superiority trial). Since there are no previous data supporting the combination use of moxibustion and TCM decoction, the sample size calculation was simply based on MD/MP group versus control group, assuming that the effect of combination treatment is equivalent to or better than moxibustion or decoction alone. Considering patient enrolment at a ratio of 1:1:1 for the control, MD, and MP groups, the sample size is calculated by multiple sample rate comparisons. The sample content estimation formula is as previously described [31]. Given that *α* = 0.05 and 1-*β* = 0.08, taking a 20% drop rate into account, the required total sample size is 462 cases and 154 cases in each group.

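### No concomitant care is prohibited, although control is defined by receiving neither decoction nor moxibustion and MP by placebo decoction: outside use should be expressly barred and recorded

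*Protocol article*

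**What the plan says.** On concomitant care {11d} the Protocol article has a single sentence: "No specific concomitant care and interventions are permitted or prohibited during the trial".

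The arms are defined by the presence or absence of two treatments. Under choice of comparators {6b}: "The control group is treated routinely without either TCM decoction or moxibustion". Trial design {8} defines control in the same way. Both other arms receive moxibustion; MD adds the active decoction, "while TCM placebo is provided to the patients in the MP group".

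Other places that bear on outside use:

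- Eligibility criteria {10} have no criterion on prior or concurrent Chinese medicine or moxibustion.
- Strategies to improve adherence {11c} covers study supplies only: moxa sticks and granules "will be provided by the Central Pharmacy of Yueyang Hospital to the corresponding participants".
- The baseline list and the schedule of enrolment and assessment (Table 3) have no item for outside TCM or concomitant medication. The schedule does list audit and ombudsman review of medical records during chemotherapy and at each follow-up.
- Section {20c} defines ITT as all eligible participants and PP as those who completed the trial.
- Blinding {17a} covers MD and MP participants only, and only for the decoction.

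**The concern.** The trial aims to show efficacy against a comparator without these treatments, and the rule on concomitant care leaves open the very treatments that separate the arms. Outside use is plausible on the document's own description: control patients know that they receive neither treatment, the single site is an integrated Chinese and Western medicine hospital, and trial moxibustion is carried out by patients at home.

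If control patients obtain treatment that works, MD versus control and MP versus control both shrink. If MP patients obtain an effective decoction, MD versus MP shrinks while MP versus control grows, so moxibustion would be credited with part of the decoction's effect. If an outside product lowered blood counts, these directions would reverse. ITT would still estimate the effect of offering treatment. But without a rule and a record, a reader of a small difference could not judge whether the treatment is weak or the comparator diluted.

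**Working it through.** **1. The plan's own figure.** Sample size {14} reports that "the bone marrow suppression rate (grade 2 or above) was 52% and 81% for the MD group and the control group, respectively", with a superiority margin of 15 points, α = 0.05, 20% dropout and 154 per arm. A margin-based formula with unpooled variance, one-sided α and power 0.80 reproduces this:

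n = [0.81×0.19 + 0.52×0.48] × (1.645 + 0.842)² / (0.29 − 0.15)² = 127.3, so 128; 128 × 1.2 = 153.6, so 154; 3 × 154 = 462.

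This reads the printed 1−β of 0.08 as 0.80. That misprint, and one-sided sizing beside two-sided analysis, are separate matters.

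**2. Inputs for the illustration.**

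- Rates: control 0.81, MD 0.52, the sizing endpoint (grade 2 or above). It is not among the listed primary outcomes, the first of which is "The proportion of patients with relief of leukopenia and/or neutropenia"; the article gives no assumed rates for those on which to repeat the calculation.
- Evaluable patients per arm: 154 × 0.8 = 123.
- c, the share of control patients using outside treatment: not in the document. Assumed 10, 20 and 30%.
- f, the share of the 29-point MD effect that a user obtains: assumed 1 (an extreme case), 0.5, or a decoction-alone value. The last comes from {14}, which says that in previous studies "the incidence rate of myelosuppression was 81.0% in the control group and 61.7% in the TCM decoction group": (81.0 − 61.7)/29 = 19.3/29 = 0.67. The grade in that source is not stated.

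**3. Formulas.** Control rate p = 0.81 − c × f × 0.29. Difference d = p − 0.52. Standard error se = √{[p(1−p) + 0.52×0.48]/123}. Two-sided 5% power = Φ(d/se − 1.96), with no margin, since {20a} plans ordinary two-sided tests.

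Worked example with f = 1, c = 0.3: p = 0.81 − 0.087 = 0.723; d = 0.203; se = √(0.4499/123) = 0.0605; power = Φ(3.36 − 1.96) = 0.919.

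**4. Results, MD versus control.**

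| Effect obtained by users | c = 10% | c = 20% | c = 30% |
|---|---|---|---|
| Full MD effect (f = 1): difference, points | 26.1 | 23.2 | 20.3 |
| power | 0.994 | 0.974 | 0.919 |
| Decoction alone (f = 0.67): difference, points | 27.1 | 25.1 | 23.2 |
| power | 0.997 | 0.990 | 0.974 |
| Half effect (f = 0.5): difference, points | 27.6 | 26.1 | 24.7 |
| power | 0.997 | 0.994 | 0.987 |

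With no outside use the difference is 29.0 points and power 0.999. The loss therefore runs from 1.5 to 8.7 points, against a 95% confidence interval half-width of 11.2 to 11.9 points. The lowest power is 0.919, or 0.913 by an exact calculation for the chi-square test; with 128 per arm it is 0.928.

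**5. The other contrasts.** The article gives no MP rate for this endpoint, so only the multiplier 1 − c×f can be stated, with f now the share of that contrast's own effect. It runs from 0.95 (c = 10%, f = 0.5) to 0.70 (c = 30%, f = 1). It applies to MP versus control for use in control, and to MD versus MP for decoction use in MP.

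**The case against.** The strongest reply is that concomitant care means care alongside the allocated treatments. Decoction and moxibustion are the allocated treatments, and {6b} and {8} already fix them by arm, so a control patient who uses moxibustion departs from the arm definition whatever {11d} says. That reading is fair, and the definitions may well imply abstention. What remains is that the one sentence meant to settle the matter prohibits nothing, and no other section shown says expressly that outside use is barred.

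The second reply is that this is a condensed article. The case report form and the full protocol (v2.1) are not shown, and medical records are audited throughout. A reader might infer that outside use would go undetected, or that it is occurring. The document supports neither: no section reports use or a rate, and use may be captured in material not shown. Detailed PP exclusions may likewise stand in an analysis plan; the point here is only that PP as worded would retain a completer who used outside treatment.

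The third reply is that the harm is hypothetical and modest. That stands for power. A reader might infer a serious power loss, because against the 15-point sizing margin (one-sided 5%, 128 per arm, users obtaining the full MD effect) power falls from 80% to 62, 41 and 23% at 10, 20 and 30% use. But {20a} plans two-sided tests and states no margin for analysis, so this would apply only if the margin were carried into the analysis. Use of an effective product in control would also not create a false superiority claim for MD over control. The distortion of MP versus control by decoction use in MP runs the other way and is not covered by that reassurance.

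**Conclusion.** The point holds as a modest, cheaply mended weakness. The article states outright that no concomitant care is prohibited, although two of its three arms are defined by the absence of treatments that patients could obtain elsewhere, and nothing shown expressly bars such use or lists it for recording. Under assumed use of 10 to 30% in control, the 29-point sizing difference falls to between 27.6 and 20.3 points, with ordinary two-sided power at about 0.91 or above. These figures rest on assumed rates of use, assumed effects per user and an endpoint that is not a primary outcome; the lowest requires users to obtain the full MD effect. The main cost is an estimate that is harder to interpret, not a trial that lacks power. Neither actual contamination nor its undetectability is established.

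**What to change.** Amend {11d} to say that moxibustion or Chinese herbal decoction for myelosuppression, outside the allocated treatment, is not permitted during chemotherapy in arms not assigned it, and that such use counts as a protocol deviation. Record any use at each cycle in all arms and report it by arm. Keep ITT as the main analysis.

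An analysis excluding recorded users can be added, labelled supportive only. It conditions on behaviour after randomisation, so it is open to selection, and it can draw only on patients recorded after the amendment. At the date in Trial status, 218 of 462 patients were enrolled (47%), so recording from enrolment could cover at most 462 − 218 = 244.

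The cost is one amended sentence, one case report form item per cycle (if the form does not already have it) and one supportive analysis. The downsides are some recorded deviations and two eras of recording, which the report should state.
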